## Abstract

**Background:**

Persistent post-concussive symptoms (PPCS) affect up to 30% of individuals following mild traumatic brain injury. PPCS frequently includes exercise intolerance. Sub-symptom threshold aerobic exercise has been proposed as a treatment option for symptom burden and exercise intolerance in this population. The primary aim of this study is to evaluate whether a progressive, sub-symptom threshold aerobic exercise program can alleviate symptom burden in adults with PPCS.

**Methods:**

Fifty-six adults (18–65) with PPCS (>3mos-5 yrs) will be randomized into two groups: an immediate start 12-week aerobic exercise protocol (AEP) or delayed start 6-week placebo-like stretching protocol (SP), followed by AEP. Aerobic or stretching activities will be completed 5x/week for 30 mins during the intervention. Online daily activity logs will be submitted. Exercise prescriptions for the AEP will be 70–80% of heart rate at the point of symptom exacerbation achieved on a treadmill test with heart rate monitoring. Exercise prescription will be updated every 3-weeks with a repeat treadmill test. The Rivermead Post-concussion Symptom Questionnaire will be the primary outcome measure at 6 and 12-weeks of intervention. Secondary outcomes include assessments of specific symptoms (headache, quality of life, mood, anxiety, fatigue, dizziness, sleep parameters, daytime sleepiness) in addition to blood biomarkers and magnetic resonance imaging and spectroscopy data for quantification of brain metabolites including γ-aminobutyric acid (GABA), glutathione, glutamate and N-acetyl aspartate (NAA) all measured at 6 and 12-weeks of intervention.

**Discussion:**

This trial will evaluate the use of aerobic exercise as an intervention for adults with PPCS, thus expanding our knowledge of this treatment option previously studied predominantly for adolescent sport-related concussion.

**Trial registration:**

ClinicalTrials.gov - NCT03895450 (registered 2019-Feb-11).

## Background

Concussion, a term often used interchangeably with mild traumatic brain injury (mTBI), results from a biomechanical force to the head inducing a sequelae of homeostatic disruptions and biochemical alterations [1]. Of all treated brain injuries, approximately 80% are classified as mild [2]. While the majority of individuals recover from mTBI in the 10–14 day acute period [3], a minority will go on to experience persistent post-concussive symptoms (PPCS) greater than 3 months. PPCS are heterogenous, but frequently include headache, dizziness, cognitive difficulties, fatigue, low mood, anxiety, emotional lability, exercise intolerance and sleep disturbances. Headache and cognitive difficulties (poor memory, difficulty concentrating) are among the most commonly reported symptoms months to years post-mTBI [4–8], in addition to fatigue [9]. At three months post-mTBI 22–40% of individuals meet ICD-10 criteria for persistent post-concussive symptoms (PPCS) [10, 11], also termed post-concussion syndrome, and up to 33% of individuals are functionally impaired based on Glasgow Coma Score-extended criteria [12].

Consensus on return to activity following mTBI has shifted considerably in recent years. Earlier editions of concussion consensus guidelines suggested rest following mTBI until complete symptom resolution [13]. The risk of a subsequent mTBI during an acute period of physiological vulnerability, which is augmented by slower thinking and reflexes, contributed to this recommendation. Following these guidelines, the notion of “rest is best” was widely adopted and reinforced [13–16]. However, recent studies have found that after a brief period (24–48 h) of rest following mTBI, exercise below symptom threshold may improve recovery over rest [17]. A large cohort study of children and adolescents (age 5 to 17.99) recruited from the emergency department found those who participated in some type of physical activity (light aerobic exercise, sport-specific exercise, noncontact drills or full-contact practice/competition) within 7 days of injury had a lower risk of PPCS at 28 days compared to those not having participated in any physical activity [18]. With new understanding that previous rest recommendations are not always beneficial to recovery, there is a great need for trials evaluating sub-symptom threshold aerobic exercise as a treatment for individuals with PPCS.

Sub-symptom threshold aerobic exercise is aerobic activity below the heart rate (HR) at which an individual’s mTBI-related symptoms are worsened. Exercise intolerance due to autonomic dysfunction is associated with elevated cerebral blood flow and arterial carbon dioxide contributing to onset of symptom exacerbation during exercise [19]. In non-concussed individuals, aerobic exercise has been shown to improve headache frequency [20], fatigue [21], mental health [22], cognition [23] and sleep [24], all of which are characteristic of PPCS. With potential to improve many mTBI-related symptoms, aerobic exercise is a promising treatment option for PPCS, yet research has largely focussed on the pediatric sport-related concussion (SRC) population in the acute/sub-acute phase following injury [25]. Leddy and colleagues investigated a progressive sub-symptom threshold intervention acutely following SRC in adolescents (age 13 to 18). Those randomized to the aerobic exercise intervention were asymptomatic in a median of 13 days, whereas those in the stretching group recovered in a median of 17 days [26]. In another adolescent sample with 4–16 weeks of persistent symptoms Kurowski et al. compared a 9-week sub-symptom aerobic training protocol to a full-body stretching protocol [27]. A greater rate of improvement based Post Concussion Symptom Inventory scores, a measure of symptom burden, was observed in the aerobic exercise group compared to the stretching group. While aerobic exercise trials in adolescents have shown promise, a similar intervention in an adult PPCS cohort has not previously been investigated. Our study participants have heterogeneous injury etiology that is not necessarily sport-related. This study cohort can also be differentiated from previous literature due to the chronic nature of symptoms (> 3 months to years), often producing functional impairment and inability to continue with employment. There is great need for personalized, low cost, non-pharmacological interventions for this adult population with potential to treat multiple post-concussive symptoms, such as aerobic exercise.

This study will investigate the utility of sub-symptom threshold aerobic exercise for the treatment of PPCS using a randomized, placebo controlled, delayed-start design. Our specific objectives are the following:
Evaluate whether an aerobic exercise protocol (AEP) produces a clinically meaningful improvement in post-concussive symptom burden compared to a placebo-like stretching protocol (SP).Evaluate change in quality of life and specific post-concussive symptoms, including headache, mood, anxiety, fatigue, dizziness, sleep parameters and daytime sleepiness, following AEP and SP.Evaluate change in blood and imaging biomarkers of exercise in mTBI recovery following AEP and SP to better understand the mechanisms of recovery.

This trial is designed to assess measures of symptom severity and quality of life in addition to investigating the underlying mechanism of recovery following intervention. These measures may help us identify which individuals will best respond to a tailored exercise program, such as that described in this protocol.

## Methods/design

### Study design

This is a randomized control trial with an immediate start AEP group and a delayed-start SP, followed by AEP group. The SP group will act as the control group for the first 6-weeks of intervention at which time the primary outcome will be evaluated for comparison of stretching versus aerobic exercise. The study design and assessment schedule is outlined in Fig. 1. The trial protocol is registered on clinicaltrials.gov (NCT03895450).

**Fig. 1 Fig1:**
[figure not shown]
Study Design Protocol

### Study group

Subjects will be eligible to participate based on the following inclusion criteria: 1) aged 18–65 years; 2) diagnosis of mTBI based on American Congress of Rehabilitation Medicine criteria [28] 3) diagnosis of PPCS based on ICD-10 postconcussional syndrome criteria [29] for a minimum of 3 months to a maximum of 5 years; 3) exercise intolerance, described as acute exacerbation of post-concussive symptoms with exercise; 4) maintenance of a stable pharmacological regiment for a minimum of one month prior to intervention start with the requirement of maintaining this regiment for the duration of the trial. Exclusion criteria includes past medical history of other neurological condition or psychiatric condition (other than depression and/or anxiety), a prior moderate or severe traumatic brain injury, or a history of cardiopulmonary or chronic musculoskeletal condition.

### Study setting and recruitment

Participants will be recruited from the Calgary Brain Injury Program at Foothills Medical Centre, University of Calgary Sports Medicine Centre concussion clinic, Calgary Pain Program and a private physiotherapy clinic in Calgary, AB, CAN where treating physicians will obtain consent to contact. Once a participant is referred and has provided consent to contact, they will be contacted by a member of the study team to discuss participation. If the individual is interested and meets inclusion criteria, an initial assessment will be scheduled. Prior to beginning the initial assessment, participants will complete a digital informed consent.

Participants may consent for the research team to use magnetic resonance imaging (MRI) data for future studies/analysis. The consent form reads as follows: “In some cases, we may wish to use your MRI data for other research studies by members of this study team. Please check one of the boxes below: a) I do not consent to having my MRI used in other research studies in addition to this study; b) I do consent to having my MRI used in other research studies”. Following checking either option a or b, a digital signature (initials) are obtained.

### Blinding and randomization

Each participant will be randomized following screening and enrollment in the study. Participants will be randomized to either the immediate start (AEP) or delayed-start group (SP + AEP) using a computer-generated randomization sequence with block sizes of 10. Allocation details are kept in opaque envelopes and revealed sequentially. Due to the nature of the intervention only the data analyst will be blinded.

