### Interventions

#### Treatment arms

Once screening is complete and a participant is enrolled, they will be randomized to either begin the aerobic exercise protocol immediately (AEP, *n* = 28), or begin the aerobic exercise following a precursor placebo-like stretching protocol (SP, n = 28). Participants in both groups will complete a digital daily exercise diary for the duration of the protocol.

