### Sample size

A power calculation using significant outcomes for RPQ in a neurorehabilitation/exercise intervention suggested 46 participants should be included to find significant improvement, with an alpha of 0.05 and 80% power [59]. With an anticipated dropout rate of 1–5 participants per group we will recruit 56 participants for this trial.

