### Analysis

The primary clinical outcome is the RPQ at 6-weeks of intervention. For the clinical outcome measures, two separate analyses will be run:
Outcome measures will be analyzed using two-way mixed ANOVA at baseline and 6-week timepoints. Two-way mixed ANOVA allows for analysis of group by time interaction effect. If a statistically significant group by time interaction effect is detected, indicating that group effect varies with time, or time effect varies with the group, simple effect testing will be used to analyze group effect broken down by time or time effect broken down by group. Should there be missing values, generalized estimating equation analysis will be employed.Outcome measures between groups (delayed-start vs. immediate start) following the aerobic exercise intervention only will be analyzed using two-way mixed ANOVA at the three primary timepoints: baseline, 6-weeks and 12-weeks.

The HERMES MRS data will be analysed to quantify GABA and glutathione levels using Gannet3, a spectral analysis tool. The PRESS MRS data will be analyzed to quantify NAA, glutamate, creatine and choline. Metabolite levels will be compared using an ANOVA model comparing groups at each of the three timepoints (as above). Additional exploratory analyses will investigate the correlations between metabolite levels and symptom burden. Whole brain ASL data will be processed to provide quantitative maps of tissue perfusion (cerebral blood flow) and group data will be compared on a whole brain basis. If no differences are detected, regional analyses may be applied. Resting state fMRI data will investigate differences in functional connectivity between groups and time points using both independent component analysis and seed-based approaches.

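### Symptom duration spans 3 months to 5 years at entry but is in neither the allocation scheme nor the stated primary model, which may cost precision and leave a chance imbalance hard to interpret

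*Protocol article*

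**What the plan says.** All references are to the protocol article.

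- **Entry (Study group).** The PPCS diagnosis must have held "for a minimum of 3 months to a maximum of 5 years". In months that is 3 to 60, a 20-fold range. The criterion is worded as duration of PPCS, which is close to time since injury.
- **Cohort (Background).** The cohort is set apart from earlier trials by "the chronic nature of symptoms (> 3 months to years), often producing functional impairment". The recovery figures given (most recover in 10–14 days; 22–40% meet criteria at three months) stop at the point where eligibility begins.
- **Allocation (Blinding and randomization).** Participants are allocated "using a computer-generated randomization sequence with block sizes of 10". No stratification factor is named. Only the data analyst is blinded.
- **Analysis.** "The primary clinical outcome is the RPQ at 6-weeks of intervention". The first of the two planned analyses reads: "Outcome measures will be analyzed using two-way mixed ANOVA at baseline and 6-week timepoints". The fallback is: "Should there be missing values, generalized estimating equation analysis will be employed". The factors are group and time; no covariate appears in either.
- **Sample size.** The calculation gave "46 participants should be included to find significant improvement, with an alpha of 0.05 and 80% power", raised to 56 for dropout. Treatment arms gives 28 per group.

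**The concern.** How long symptoms have lasted is a plausible predictor of how much a patient's RPQ changes over the next 6 weeks. It varies widely here, and eligibility already depends on it. Blocked allocation without strata balances arm sizes but not duration, and the stated model does not remove whatever variance duration explains.

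Under Study design, the stretching arm serves as control for the first 6 weeks only. The 6-week RPQ contrast is therefore the one randomised comparison of AEP with SP. Two things are at stake in it: precision, if duration predicts change; and interpretability, if the arms happen to differ in duration. Adding the covariate only after an imbalance has been seen would look data-driven, so it should be settled beforehand.

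**Working it through.** **1. The plan's own figure.** The effect size and SD behind 46 are not given, so 46 cannot be reproduced, only back-solved. With 23 per arm, two-sided alpha 0.05 (sidedness is not stated) and 80% power, the normal approximation gives d = (1.960 + 0.842) × √(2/23) = 0.826. If the 4.6-point MCID were the target (assumption), SD = 4.6/0.826 = 5.57. The dropout step does reproduce: 46 + 2 × 5 = 56. The point made here does not alter the sample size.

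**2. What the stated test is.** With two time points, the group-by-time test is equivalent to a two-sample t test on change from baseline. Stable differences in RPQ level between short- and long-duration patients cancel. Duration matters only if it predicts 6-week change.

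**3. Chance imbalance.** Call K of the 2n patients *early* (short duration; the share is an assumption). Ignoring blocks, the number early in one arm follows P(X = x) = C(K, x) C(2n − K, n − x) / C(2n, n), and the arms differ by |2X − K| early patients. The probability of a difference of at least 20 percentage points is:

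| Early share | 28 per arm | 23 per arm |
|---|---|---|
| about 20% | 4% | 14% |
| about 30% | 8% | 11% |
| 50% | 18% | 24% |

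The pattern is uneven because only differences with the same parity as K can occur. At 28 per arm and 50% early, for example, the threshold is 6 patients (6/28 = 21 points); with K = 17 it is 7 (25 points).

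**4. Size of the shift.** Shift = imbalance × early–late gap in 6-week improvement. The gap is an assumption.

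- 0.20 × 2 = 0.4 points (0.4/4.6 = 9% of the MCID)
- 0.20 × 4 = 0.8 points (17%)
- 0.20 × 6 = 1.2 points (26%)

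**5. Error rate and power.** These come from simulation: 40,000 runs per setting, 23 per arm, 30% or 50% early, within-stratum SD of change 5.57 or 10, and a true effect of 0.826 SD. All of these settings except 23 per arm are assumptions.

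- Unconditional type I error, unadjusted: 4.9–5.1% in every setting.
- Type I error among runs with an imbalance of at least 20 points (11–24% of runs), unadjusted: 5.7–5.9% at a 2-point gap, 5.7–9.1% at 4 points, 7.0–12.9% at 6 points. Adjusted, over the same three gaps: 4.4–5.6%.

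| Gap (points) | Power, unadjusted | Power, adjusted |
|---|---|---|
| 0 | 78% | 77–78% |
| 2 | 77–78% | 77% |
| 4 | 73–77% | 77–78% |
| 6 | 68–75% | 77% |

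The base is 78% rather than 80% because d = 0.826 comes from the normal approximation and the test uses t. The largest gain is 77.3 − 67.5 = 9.8 points (gap 6, SD 5.57, 50% early). With no gap, adjustment costs about 1 point.

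**6. The strength of prognosis this implies.** For early share p, gap g and within-stratum SD s, r² = p(1 − p)g² / (s² + p(1 − p)g²). The weakest non-zero setting (p = 0.3, g = 2, s = 10) gives 0.84/100.84 = 0.008, so r = 0.09. The strongest (p = 0.5, g = 6, s = 5.57) gives 9/40.02 = 0.22, so r = 0.47. The documents do not say where the truth lies.

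**The case against.** The strongest case against has five parts.

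- **Unstratified blocked allocation is legitimate for 56 patients.** This stands. Nothing in the randomisation text needs to change.
- **A covariate list may sit in an analysis plan that is not shown.** This stands in part. An article may leave such detail out, but this one names its primary model and fallback, and a two-way group-by-time ANOVA has no place for duration. If the unseen plan already adjusts for it, one sentence reconciling the two closes the point.
- **The cohort is selected for persistence.** This stands. The Background calls it chronic, its recovery figures concern the period before eligibility, and no recovery rate after 3 months is given. Duration is a plausible prognostic factor, not a demonstrated one.
- **Every consequential number is assumed.** The early share, the gap and the SDs are assumptions, which is why ranges are shown. They include settings where adjustment gains nothing.
- **Duration in months is not listed among the baseline items under Measures.** This is true. Screening must establish that it falls within the window, so the exact value should be easy to record.

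A reader might infer something stronger: that an excess of still-recovering patients in one arm could mimic or hide an AEP effect, making the primary comparison unreliable. The document does not support this. Chance imbalance under valid randomisation is already covered by the 5% error rate, and the error rate rises only conditionally, in the minority of trials with a marked imbalance. Even there, the shift of 0.4 to 1.2 points is well below 4.6. That patients are still recovering after 3 months is not stated anywhere.

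**Conclusion.** The point holds as a modest matter of precision and conditional balance, not as a validity flaw. Duration of PPCS, with a 20-fold range at entry, is in neither the allocation scheme nor the stated primary model. The unadjusted test keeps its overall 5% error rate.

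Under the assumptions shown, a marked imbalance has a probability of 4–18% at 28 per arm and 11–24% at 23 per arm. Adjustment is worth about 10 points of power at best. It is worth nothing, or costs about 1 point, if duration does not predict 6-week change. The case for acting is that the remedy is cheap and loses its credibility if adopted after outcomes are known.

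**What to change.** In the Analysis section, before the analyst sees outcome data:

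1. Prespecify baseline symptom duration (or time since injury; choose one and define its start), in log months, as a covariate in the primary 6-week RPQ model and in the GEE fallback.
2. Enter it so that it adjusts the 6-week *change*: either a covariate-by-time term in the mixed model, or an ANCOVA on 6-week RPQ with baseline RPQ and duration as covariates. A main effect alone would leave the group-by-time test unadjusted for duration.
3. Tabulate duration at baseline by arm.
4. Record the exact value for everyone, including those already enrolled.

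Leave the randomisation as it is, since Study status says enrolment is under way. The cost is a sentence or two of text, one degree of freedom for the duration term (44 to 43 with 46 analysed) and little gain if duration turns out not to be prognostic.

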#### Stretching intervention

Participants are asked to complete a 30 min, low-intensity stretching program 5x/week for 6 weeks. A detailed program with each day’s stretches (written and figure format) will be provided. None of the stretches have neck involvement as not to exacerbate neck pain or headache symptoms. All stretches will be demonstrated by a member of the study team at the initial assessment. Participants are instructed to not exceed 50% of age predicted max HR during stretching. HR will be monitored by participants using a PolarH10 HR monitor.

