### Data management

Participants will be assigned a study ID number at the time of randomization by which they will be identified within the research team. Study data will be entered into a highly secure electronic REDCap database which requires double password protection to enter. Only research team members will have access to this database. Participant information or other data transmitted through USB will be encrypted. USB transfer of information will only be used when absolutely necessary and will be password protected. Paper copies of any data or participant information will be kept in a locked cabinet in a locked room in a locked university building.

All identifying information will be removed once all study participant numbers have been assigned and all data is collected. When data is downloaded for analysis, manuscript writing or abstract preparation all identifying information will be excluded. This information will be downloaded to a password protected SPSS file for analysis. No identifiable information will be retained once data collection is complete. All data will be retained for five years following project completion in accordance with Health Canada retention guidelines.

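### A single fixed block size of 10, reported during recruitment in an open-label trial, makes about 15% of allocations knowable in advance to anyone who keeps count

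*Protocol article*

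**What the plan says.** The Blinding and randomization section of the protocol article gives the rule for allocation and concealment: participants are allocated "using a computer-generated randomization sequence with block sizes of 10. Allocation details are kept in opaque envelopes and revealed sequentially". On blinding it says "Due to the nature of the intervention only the data analyst will be blinded". On timing it says "Each participant will be randomized following screening and enrollment in the study".

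Three other sections bear on the point:

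- Treatment arms and Sample size give 28 per arm and 56 in total, so allocation is 1:1. No stratification is mentioned.
- Study setting and recruitment says that treating physicians obtain consent to contact. A member of the study team then contacts the person, and an initial assessment is scheduled if the person is interested and eligible.
- Study status says that recruitment and enrollment were under way when the article was submitted.

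The article does not say who generated the list, who holds or opens the envelopes, or which staff know the block size.

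**The concern.** In a permuted block the two arms must come out equal, so the last places are forced once one arm is full. This matters little when past allocations are hidden or the block length is unknown. Here the length is one number, stated in a public article, and the participants and staff are not blinded, so past allocations are visible to those who deliver or discuss the programmes.

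Study-team members also contact referred patients and book the first visit. A person who knew that the next place was aerobic exercise could, even unintentionally, hurry or delay a particular patient. Eligibility leaves some room for judgement: exercise intolerance is described in the Study group section without a numerical threshold. The result would be selection bias, with arms that differ systematically at entry. The primary outcome is a self-reported questionnaire from unblinded participants, and blinding the analyst does not correct for who entered which arm.

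**Working it through.** **Inputs.** Block size 10, allocated 5:5 (Blinding and randomization; Treatment arms). Total 56 (Sample size). One sequence for the whole trial is assumed, because no stratification is mentioned.

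**The plan's own figure.** The article gives no predictability figure. Its total is reproduced by adding the upper end of the stated dropout range to the powered number: 46 + 2 × 5 = 56.

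**Certain allocations in one block.** Place *k* is certain when one arm already holds all 5 of its places among the first *k* − 1. The probability is 2 × C(*k* − 1, 5) / C(10, 5), with C(10, 5) = 252.

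| Place in block | Calculation | Probability that it is certain |
|---|---|---|
| 1 to 5 | – | 0 |
| 6 | 2/252 | 0.8% |
| 7 | 12/252 | 4.8% |
| 8 | 42/252 | 16.7% |
| 9 | 112/252 | 44.4% |
| 10 | 252/252 | 100% |

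The sum is 420/252 = 1.667 per complete block. This agrees with the general result 2*m*/(*m* + 1) for a block of 2*m*: 10/6 = 1.667.

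**Whole trial.** 56 places are five complete blocks and the first six places of a sixth: 5 × 1.667 + 0.008 = 8.34, and 8.34/56 = 14.9%. A simulation gave 15.0%. The 10th, 20th, 30th, 40th and 50th allocations are always among the certain ones.

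**Best guess.** Always naming the arm with more places left is right, per complete block, 5 + 2⁹/252 − 0.5 = 6.53 times in 10. Over 56 places, by exact enumeration, it is right 36.10 times: 36.10/56 = 64.5%, against 50% by chance.

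**Sensitivity of the 14.9%.** With 46 participants it is 14.5%, and with 60 it is 16.7%. If there were four separate sequences of 14 (an assumption; the article describes none), it would be 4 × 1.667/56 = 11.9%.

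**Is 10 too small?** No. Fixed blocks of 4, 6 or 8 over 56 participants would make 33.3%, 24.1% or 20.0% certain. The weakness is one known size in an open trial.

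**What varying the size achieves.** The sizes below are illustrative, since the article gives none. Each size is equally likely, and the observer knows the set of sizes but not their order (1,500 simulated lists each).

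| Scheme | Certain of 56 | Share | Best guess correct |
|---|---|---|---|
| Fixed 10 (exact) | 8.34 | 14.9% | 64.5% |
| Random 4/6/8 | 1.18 | 2.1% | about 68% |
| Random 6/8/10 | 0.94 | 1.7% | 66.0% |

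Varying the size removes most of the certainty but does not lower the rate of correct guessing.

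**The case against.** The best defence is that the 15% is a capability, not an event. It needs a person who has both the block size and a complete running count, and who also influences which patient comes next. The article does not say that any one person has all three. Referrals come from physicians in several settings, and nothing suggests that they see allocations. Ten is also a fairly large block for this trial, and replacing the list would not lower the best-guess rate. All of this stands and limits the weight of the point. It does not remove it: the size is in print, allocations are open, and study-team members do contact and schedule participants.

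Two stronger readings are tempting, and the article supports neither.

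- **That the baseline symptom score is reported after the participant knows the arm.** A reader might infer this from "All stretches will be demonstrated by a member of the study team at the initial assessment" and "Participants will be assigned a study ID number at the time of randomization". Both sentences fit the other order equally well: baseline questionnaires and treadmill test first, then the envelope, then teaching at the end of the same visit. In the aerobic arm the prescription depends on the heart rate reached on the treadmill test, so that instruction must come after the test. The assessment schedule is in Fig. 1, which was not available here, and visit order is something a condensed article can leave to the full protocol.
- **That the scheme fails because 56 is not a multiple of 10.** An exact 28:28 split has probability C(6,3) × C(4,2)/252 = 120/252 = 47.6%. However, the worst possible split is 30:26, with relative efficiency 4 × 30 × 26/56² = 3120/3136 = 99.5%. This is harmless.

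**Conclusion.** The point holds as a moderate weakness in allocation concealment. With one sequence of fixed blocks of 10, about 8.3 of 56 allocations (15%) are certain, before the envelope is opened, to anyone who knows the block size and keeps count. The same person's best guess would be right 64.5% of the time overall.

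This rests on three assumptions: a single unstratified list, 5:5 allocation within each block, and at least one person who has both the size and the count and has some say over who is booked next. The first two follow from the article's wording or its silence on strata. The third is possible under the arrangements described but is not shown.

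No bias in the treatment effect is estimated, because nothing in the article allows it. No claim is made that any allocation was predicted or misused, or that baseline reporting was affected by knowledge of the arm.

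**What to change.** For participants not yet randomized, replace the list with one that uses randomly varying block sizes. Record the sizes in a restricted file and disclose them only after recruitment closes. Someone outside the team that contacts and schedules participants should prepare and hold the list. This separation matters as much as the new sizes: varying them cuts certain allocations to about 2%, but guessing remains above chance at about 66–68%.

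As a safeguard, open each envelope only after the baseline questionnaires and treadmill test have been submitted. If this is already the practice, one sentence in the article or full protocol is enough.

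The cost is one new list and an independent holder for it, with no extra visits. The downside is a change of list part-way through recruitment. It should be documented with its date and the number randomized under each list. It cannot improve concealment for participants already allocated.
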